### Demographic variables and descriptive

We will record the following variables: age, living alone (yes/no), BMI, smoking (yes/no), are you afraid of falling (yes/no), have you fallen the last year (yes/no), injuries caused by falls the last year, number and name of medications, taking analgesics (yes/no), pain level last week by score from 0 to 10 on a Numeric Rating Scale [30, 31] and comorbidities.

### Primary outcome

Physical function, measured by 10 m habitual walking speed, is the primary outcome of this study. Walking speed is considered as a robust measure and is a valid, reliable and sensitive measure for assessing functional status and overall health in a wide range of populations [32, 33]. Walking speed is indicative of an individual’s functional capacity and general health status, but also predictive of a range of outcomes including rehabilitation response, frailty and mobility disability. There is also an observed association between slow selected walking speed and lower quality of life [32, 34].

There is no standardized protocol available for measuring walking speed, and a variety of procedures exist that differ in regards to distance [32, 35]. In this study habitual walking speed of a straight path of 10 m will be measured from a static position, using a stopwatch as timing instrument. No acceleration or deceleration phase will be used. The stopwatch is started as the participant crosses the start line with her first foot, and stopped when crossing the finishing line with the first foot [35]. The participant will be instructed to walk at a comfortable pace, in the speed she normally chooses when walking from one point to another. A walking aid can be used when necessary, and the test will be performed with the same walking aid at the post tests if needed.

### Secondary outcomes

Secondary outcomes are physical fitness, HRQOL, Falls-efficacy Scale International (FES-1) and International Physical Activity Questionnaire short form (IPAQ –SF).

#### Physical fitness

Alongside habitual walking speed as a measure of physical fitness, we apply tests like functional reach (FR), the four square step test (FSST), grip strength and Senior Fitness Test (SFT).

FR is a reliable and valid measure of proactive balance [36], and is a sensitive measure strongly connected to physical frailty [37]. FR is a measure of the maximal distance one can reach forward from a standing static position. The test will be performed three times, after one test trial to make sure that the participant understands the instructions. A mean of three recorded attempts will be reported.

FSST is a balance test for dynamic standing balance [38]. Four sticks or canes are resting on the floor forming four squares. The participant is instructed to step as fast as she can from square to square, with both feet resting in one square before she can move to the next. The FSST will be performed starting in square 1 then moving to 2,3,4,1,4,3,2,1. This test requires that the participant steps forward, backward and sideways, both to the left and right. A stopwatch is used to measure time it takes to complete, starting when the first foot touches square 2 and stops when the last foot has landed in square 1. The participant will first be shown the test, before one trial attempt is performed. The best of two successful attempts will be recorded as the score. Tested on a group of community dwelling elderly adults, the FSST is shown to be valid and reliable test, with a sensitivity of 85% and a specificity of 88–100% [38].

Grip strength is measured with a hydraulic handheld dynamometer, using the second position of the handle position for all participants. The handgrip test is a simple and reliable [39] method of measuring muscle strength [40]. Grip strength measurement has shown to have predictive validity, and falls, disability, low health related quality of life have been associated with low values of grip strength [40]. The test will be performed with the subject sitting at a chair, holding the instrument with the shoulder in a neutral position, elbow flexed to 90 degrees. The participant will perform one submaximal test of each hand, before performing three maximal tests of each side. The dominant hand will be tested first. The highest score of each hand is recorded.

SFT is a valid and reliable test for physical fitness [41] designed to assess underlying physical components associated with mobility in older people, such as muscle strength, aerobic endurance, flexibility, body composition (assessed as BMI in kg/m2) and agility/dynamic balance [42]. The test consists of: number of Chair Stands in 30 s, number of Arm Curls in 30 s, Chair-Sit-and-Reach-Test (CSRT) (cm), Back Scratch Test (cm), 2.45 m Up-and-Go test (seconds) and 6 min walk test (6 MWT) and BMI (weight/height^2^). All of the tests have high reliability and validity and the procedures for administering SFT are standardized and described in detail [41, 42]. The CSRT was excluded due to safety reasons for our study population, as it requires flexion of the back. The 6 MWT will of practical reasons be performed walking around a 40 m course. In a study from Sciurba et al. [43] there was reported no significant difference between walking courses of 15 to 50 m.

#### Health-related quality of life

HRQOL will be measured by the Quality of Life Questionnaire of the European Foundation for Osteoporosis (QUALEFFO-41) which is a disease-specific self-reported quality of life questionnaire containing 41 questions or items in five sections; pain, physical function, social function, perception of general health and mental function. These five sections can be evaluated separately or represented in a total score of all the 41 items [7]. Futhermore HR-QoL will also be measured by the Short Form 36 (SF-36). The SF-36 is divided into eight sub-scales (physical function, role limitations-physical, bodily pain, general health, vitality, social function, role limitations-emotional and mental health). The instrument is scored to a 0–100 scale for each sub-scale, the higher the score, the better the health status [44]. The SF-36 is shown to have high reliability and validity among older people [45].

#### Fear of falling

The Norwegian version of the Falls-Efficacy Scale international (FES-I) [46, 47] will be used to examine fear of falling. The FES-I assesses level of concern about falling on a 4 point scale during 16 activities of daily living. Scores range from 16 to 64 with higher scores indicating greater concern about falling.

#### Physical activity

To measure level of physical activity we will use the International Physical Activity Questionnaire Short Form (IPAQ –SF). IPAQ-SF measures self reported physical activity over the previous 7 days. It records 4 levels of physical activity; vigorous- intensity, moderate intensity, walking and sitting. The IPAQ-SF is frequently used as a measure of physical activity and is reported to have high reliability [48], its validity against objective measures of physical activity is questioned by Lee et al. [49].

### Adherence

Adherence will be calculated as the percentage completed of the total intervention days prescribed (24 sessions = 100%).

### Sample size estimation

The sample size is based on a substantial meaningful change in 10 m habitual walking speed [50]. Perera [50] defined the minimal detectable change as 0.05 m/s. A substantial meaningful change is defined as 0.10 m/s and the expected standard deviation in habitual walking speed is assumed to be 0.2 m/s based on findings by Perera [50]. This estimate requires 128 patients, 64 in each group, to obtain 80% statistical power with 5% significance level for an independent samples t-test. We will aim to include 150 in order to compensate for an estimate of 20% drop outs.

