**Methods:**

The study is a single-blinded randomized controlled trial. Women aged 65 years or older with osteoporosis and a history of vertebral fracture are included. The intervention group receives a 12-week multicomponent exercise programme, including resistance training combined with balance training. The control group receives usual care. Adherence to the programme will be of importance for the internal validity of the study. Participants in the exercise group who don’t attend will be followed up with motivational phone calls. The primary outcome is habitual walking speed over 10 m. Secondary outcomes are health related quality of life (Qualeffo-41, SF-36), physical activity (I-PAQ), Patient Specific Functional Scale, Fear of falling (FES-1) and physical fitness (Senior Fitness test, Functional reach test, 4 square step test, grip strength). Sample size, based on the primary outcome, is 150 participants randomized into the two arms on a 1:1 allocation, including an estimated 20% drop out. Descriptive data will be reported as mean (standard deviation), median (range) or count (percent) as appropriate. The data will be analysed following the intention-to-treat principle. Between group differences in primary and secondary outcomes at 3 months follow-up will be assessed using linear regression models with respective outcome at baseline as covariate and the randomised group as factor.

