### Statistical procedure

The results of the study will be reported in accordance with CONSORT [51]. Statistical analysis is performed using statistical software as e.g. SPSS, Stata or R. The level of significance is 5%. Descriptive data will be reported as mean (standard deviation), median (range) or count (percent) as appropriate. The data will be analysed following the intention-to-treat principle. Between group differences in primary and secondary outcomes at 3 months follow-up will be assessed using linear regression models with respective outcome at baseline as covariate and the randomised group as factor (dummy variable), i.e. an ANCOVA analysis [52]. In addition, we will perform linear mixed model analysis for repeated measurements. We expect few or none missing data in baseline characteristics. However, due to possible drop-outs or participants unable to complete the outcome measurements, there might be missing data for both primary and secondary outcomes during follow-up. Linear mixed model for repeated measurement is able to statistically adjust for missing data associated with variables in the model, i.e. missing at random (MAR) structure. Further, we will also assess multiple imputation methods and sensitivity analysis for missing data in longitudinal studies. All tests will be two-sided. A statistical analysis plan will be performed in advance of each paper from the study.

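### A target of 150 does not cover the plan's own 20% drop-out: 120 would remain against the 128 required, and t-test power would be 77.5%, not 80%.

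*Protocol article*

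**What the plan says.** In the protocol article, under Sample size estimation, the calculation rests on a target difference ("A substantial meaningful change is defined as 0.10 m/s") and a standard deviation ("the expected standard deviation in habitual walking speed is assumed to be 0.2 m/s"). The result is: "This estimate requires 128 patients, 64 in each group, to obtain 80% statistical power with 5% significance level". The test named there is the independent samples t-test, and the Statistical procedure section adds: "All tests will be two-sided".

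The recruitment target follows: "We will aim to include 150 in order to compensate for an estimate of 20% drop outs". The Methods part of the abstract repeats it, saying that the sample size "is 150 participants randomized into the two arms on a 1:1 allocation, including an estimated 20% drop out".

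No other rule for inflating the sample size appears. For the between-group comparison at 3 months, the Statistical procedure section plans a linear regression with the baseline value as covariate (ANCOVA). It adds a linear mixed model, and multiple imputation and sensitivity analyses for missing data. The sample size calculation takes no credit for any of these.

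**The concern.** Three stated figures have to fit together: 128 evaluable women for 80% power, 20% drop-out, and 150 randomised. They do not, because 80% of 150 is less than 128. One of the three must give way, and the text does not say which.

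This sentence is the only justification given for the size of the trial on its primary outcome. The Limitations section concedes that an effect on walking speed may be harder to show because slow walkers are not specifically recruited, and it names drop-out as a risk. If the result is null, a reader would take from the article that the trial kept 80% power after losing a fifth of its participants. On the stated basis it would not.

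**Working it through.** **Inputs**

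| Input | Value | Source |
|---|---|---|
| Difference | 0.10 m/s | Sample size estimation |
| Standard deviation | 0.2 m/s | Sample size estimation |
| Test, power, level | t-test, 80%, 5% | Sample size estimation |
| Sidedness | two-sided | Statistical procedure |
| Allocation | 1:1 | Study design |
| Drop-out and target | 20%, 150 | Sample size estimation; abstract |

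**Step 1: the plan's 128.** The standardised difference is d = 0.10/0.2 = 0.5. With n per group, the t statistic has 2n − 2 degrees of freedom and noncentrality d/√(2/n). Solving for 80% power gives n = 63.77, rounded up to 64. At n = 64 the noncentrality is 0.5/√(2/64) = 2.83 and the power is 80.1%. The 128 reproduces.

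**Step 2: the inflation.**
- Randomised number needed to keep 128 after 20% loss: 128/(1 − 0.20) = 160.
- Remaining from 150 after 20% loss: 150 × 0.80 = 120, or 60 per group, eight short of 128.
- Largest loss that 150 can absorb: 1 − 128/150 = 14.7%.
- A common but wrong rule, adding 20% to 128, gives 128 × 1.2 = 153.6, or 154. Rounding down might explain 150, but 20% loss would still leave only 120.

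**Step 3: t-test power with 60 per group.** The noncentrality is 0.5/√(2/60) = 2.74 with 118 degrees of freedom, and the power is 77.5%. The normal approximation gives 78.2%. The difference detectable with 80% power is 0.103 m/s, against 0.100 m/s with 64 per group.

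**Step 4: the planned ANCOVA with 60 per group.** Adjustment for baseline reduces the standard deviation to 0.2 × √(1 − r²), where r is the correlation between baseline and 3-month walking speed. The document gives no value of r, so these are assumptions:

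| r | Adjusted SD (m/s) | Power, 60 per group |
|---|---|---|
| 0 | 0.200 | 77.5% |
| 0.20 | 0.196 | 79.2% |
| 0.25 | 0.194 | 80.1% |
| 0.30 | 0.191 | 81.3% |
| 0.50 | 0.173 | 88.0% |
| 0.70 | 0.143 | 96.7% |

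The 80% mark is crossed at r of about 0.245. The table keeps 118 degrees of freedom; the one used by the covariate makes no material difference.

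**The case against.** Nobody can rescue the sum itself, but there is a fair case that it matters little.

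- **The planned test is not the t-test.** The 77.5% belongs to an unadjusted comparison, and the ANCOVA falls below 80% only if r is under about 0.25. This stands as mitigation. It does not make the sentence true, because the calculation names the t-test and states no correlation. Sizing on a t-test and analysing by ANCOVA is a common conservative choice and is no fault here.
- **The loss is smaller than the uncertainty in the standard deviation.** With 0.21 instead of 0.20 m/s, power at the full 64 per group would be 76.2%, a larger drop than the one found here. This also stands, and it limits the weight of the point.
- **The 20% may mean loss by 6 months.** The main comparison is at 3 months, when fewer may have left; with 15% loss from 150, t-test power is 80.0%, and with 17% it is 79.0%. The text does not say which time point it means, so 120 at 3 months is the less favourable reading. Under either reading, 20% loss from 150 leaves 120, so the claim that 150 covers it fails.
- **Mixed models and imputation deal with drop-out.** They address missing data under a missing-at-random assumption. They do not restore the outcomes of women who leave before the 3-month visit, and the sample size does not rely on them.
- **A null result would be read from its confidence interval.** Largely so, and a shift of 0.003 m/s would not change that reading. The published power statement is still wrong.

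**Conclusion.** The concern holds. With 150 randomised, the stated 80% power and the stated 20% drop-out cannot both be true on the stated t-test basis. The shortfall is 8 evaluable women (120 against 128), or 10 randomised (150 against 160). Power is 77.5% instead of 80%, and 150 covers 14.7% drop-out. These figures use the document's own difference, standard deviation, level and test, and assume that losses are equal in the two groups and already present at the time point analysed.

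The practical effect is small, and nil if the baseline to 3-month correlation is about 0.25 or more under the planned ANCOVA. This is an error in the stated justification, made in the sample size section and repeated in the abstract. It does not show that the planned analysis is underpowered.

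**What to change.** Keep 150 and drop the claim that it compensates for 20% under the t-test, in both the Sample size estimation section and the abstract. Replace it in one of two ways:

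1. **Stay with the t-test.** State that 150 allows for 14.7% drop-out, and that with 20% drop-out 120 remain and t-test power is 77.5%.
2. **Use the planned ANCOVA.** State the assumed correlation between baseline and 3-month walking speed with its source, and show that 120 evaluable women give at least 80% power for r of 0.25 or more.

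In either case, say whether the drop-out figure refers to 3 or 6 months. Raising the target to 160 would also make the sum correct, but it means ten more participants when recruitment is planned to end in spring 2018, and the size of the shortfall does not call for it.

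The cost is two sentences of text, with no change to recruitment, conduct or analysis. The stated power becomes slightly less favourable, or it rests on a correlation that readers can judge.

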### Statistical procedure

The results of the study will be reported in accordance with CONSORT [51]. Statistical analysis is performed using statistical software as e.g. SPSS, Stata or R. The level of significance is 5%. Descriptive data will be reported as mean (standard deviation), median (range) or count (percent) as appropriate. The data will be analysed following the intention-to-treat principle. Between group differences in primary and secondary outcomes at 3 months follow-up will be assessed using linear regression models with respective outcome at baseline as covariate and the randomised group as factor (dummy variable), i.e. an ANCOVA analysis [52]. In addition, we will perform linear mixed model analysis for repeated measurements. We expect few or none missing data in baseline characteristics. However, due to possible drop-outs or participants unable to complete the outcome measurements, there might be missing data for both primary and secondary outcomes during follow-up. Linear mixed model for repeated measurement is able to statistically adjust for missing data associated with variables in the model, i.e. missing at random (MAR) structure. Further, we will also assess multiple imputation methods and sensitivity analysis for missing data in longitudinal studies. All tests will be two-sided. A statistical analysis plan will be performed in advance of each paper from the study.

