### Study setting

The present study will be undertaken at facilities in Oslo and Akershus University College of Applied Sciences, and at two different community based facilities in the area around Oslo, Norway.

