The programme will last for 1 h and will be carried out twice a week for 12 weeks. The physiotherapist supervising the exercise session, will also be responsible for individual tailoring and suitable dosage and progression of the exercises. The exercise session starts with 10 min warm up consisting of stretching, breathing exercises, flexibility and dynamic balance carried out with background music. The warm up is followed by two rounds of stationary circuit sessions with strength- and balance exercises. The participants will work 1.5 min at each station, with a short break of 30 s to rest and move to the next station. The exercise session ends with 10 min cool down and stretching. The participants are encouraged to report any serious adverse events caused by the exercise like muscle soreness, joint tenderness and increased level of pain.

When designing the exercise programme all the chosen exercises were evaluated according to safety cautions for people with osteoporosis and vertebral fractures [3, 18, 21]. Exercises that includes flexion and rotation of the spine are not considered safe and therefore not included in the programme. We also had in mind that the participants should be able to support themselves on a chair or a bar when performing exercises that challenged the balance if needed. Correct techniques in the different exercises is also a priority in the programme, and for the two first weeks of the programme this is emphasized for the participants by thoroughly instructions of the physiotherapists. The exercise group will have no more than 8–10 participants at the time, making sure that the physiotherapist can supervise and instruct the participants in a safe way. After a few weeks of adaption, the participants are encouraged to intensify their exercise and work until volitional fatigue without jeopardizing safety so that they perceive it as somewhat hard. This corresponds with an intensity level of 13–14 on the Borg Rating of Perceived Exertion Scale [28]. Weight belts, elastic bands, manual weights and frequency will be used for the progression of the strength exercises. Advancing to more challenging positions will be used to progress in balance exercises [29]. See Table 1 for a detailed description of the exercises.

**Table 1 Tab1:** Resistance and balance programme, description of exercises

Exercise	Therapeutic goal	Level	Description	Progression or modify
Squats	Leg strength	1	Raise from a chair (sit to stand)	Tempo, weightbelt

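### Only the exercise arm is treated in shared classes, yet the ANCOVA and the sample size treat all women as independent; if outcomes correlate within class, the 5% test is liberal

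*Protocol article*

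**What the plan says.** **Delivery.** Under Study design, women are allocated individually, 1:1. Under Intervention group, the programme is a group-based circuit led by a physiotherapist, with a cap on class size: "The exercise group will have no more than 8–10 participants at the time". The same section makes the instructor responsible for dose: "The physiotherapist supervising the exercise session, will also be responsible for individual tailoring and suitable dosage and progression of the exercises". Under Study setting, the trial runs at the university college and "at two different community based facilities in the area around Oslo, Norway". Under Control group, the comparison arm receives usual care, and no grouping is described.

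**Analysis.** Statistical procedure specifies, for the primary and all secondary outcomes at 3 months, "linear regression models with respective outcome at baseline as covariate and the randomised group as factor (dummy variable), i.e. an ANCOVA analysis". It also says "All tests will be two-sided", at the 5% level. A linear mixed model for repeated measurements is added and is justified by its handling of missing data. No class, instructor or facility term is named.

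**Sample size.** 64 women per group are planned "to obtain 80% statistical power with 5% significance level for an independent samples t-test". There is no design effect and no ICC. The Limitations section does not mention clustering.

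**The concern.** This is an individually randomised trial with group treatment in one arm. Women in the same class share an instructor who steers dosage and progression, and they share the class itself. Controls share nothing comparable. If some classes work better than others, the outcomes of classmates are correlated after adjustment for baseline. The exercise-arm mean is then less precise than an independence model assumes.

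The consequence is a standard error that is too small, an interval that is too narrow, and a nominal 5% test that rejects too often. It reaches every outcome, because the same model is stated for all of them. The sample size rests on the same assumption.

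**Working it through.** **Inputs from the protocol article.** Two-sided alpha 5%; difference 0.10 m/s ("A substantial meaningful change is defined as 0.10 m/s"); SD 0.2 m/s; 64 per group; class size m at most 8–10.

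**Assumed.** ICC 0 to 0.10, because none is given. For the ANCOVA, the relevant ICC is that of the baseline-adjusted outcome.

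**1. The plan's own figure.** A two-sided 5% t-test for 0.10 m/s with SD 0.2 needs 63.8, so 64 per group. Power at 64 is 80.1%. The figure reproduces under independence.

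**2. Clustering in one arm.** The exercise-arm variance is multiplied by DE = 1 + (m − 1) × ICC, and the control-arm variance is unchanged. Hence

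- true SE / model SE = √[(DE + 1)/2]
- true alpha = 2 × [1 − Φ(1.96 / ratio)]

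Example, m = 10 and ICC 0.05: DE = 1 + 9 × 0.05 = 1.45; ratio = √(2.45/2) = 1.107; 1.96/1.107 = 1.771; true alpha = 7.7%.

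**3. Closed classes of 8–10, 64 per group.** The unadjusted model SE is 0.2 × √(2/64) = 0.0354 m/s. Power is by normal approximation, which gives 80.7% at ICC 0.

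| ICC | SE ratio | True alpha | Power, t-test basis |
|---|---|---|---|
| 0 | 1.00 | 5.0% | 80–81% |
| 0.01 | 1.02 | 5.4–5.5% | 79% |
| 0.02 | 1.03–1.04 | 5.8–6.0% | 77–78% |
| 0.05 | 1.08–1.11 | 7.1–7.7% | 72–74% |
| 0.10 | 1.16–1.20 | 9.2–10.4% | 65–68% |

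Simulating the stated ANCOVA (10,000 runs per setting, 64 per arm, assumed baseline correlation 0.7) gave rejection rates of 4.7–5.1% at ICC 0, 5.4–5.8% at 0.01, 5.8–5.9% at 0.02, 7.0–7.5% at 0.05 and 9.3–10.3% at 0.10. This agrees with the formula.

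**4. Rolling entry.** The article does not say whether classes are closed. Recruitment runs from January 2016 to spring 2018, taken here as 28 months or about 121 weeks. Under Outcome measures, the intervention should start within about two weeks of baseline. With 75 exercisers for 12 weeks each, 75 × 12 / 121 ≈ 7.4 women exercise at any one time. Spread evenly over three facilities, that is about 2.5 each. Effective cluster sizes of 2.5 (no overlap) to 5 (partial overlap) give:

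| ICC | m = 2.5 | m = 5 |
|---|---|---|
| 0.02 | 5.2% | 5.5% |
| 0.05 | 5.4% | 6.2% |
| 0.10 | 5.9% | 7.4% |

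An uneven spread, or one instructor leading several classes, would enlarge the clusters.

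**5. Power under the planned ANCOVA.** Multiplying the SD by √(1 − r²), with 64 per group and m = 8–10, gives power at ICC 0.02 / 0.05 / 0.10 of about 97% / 95% / 91–93% for an assumed r = 0.7, and 88% / 84–85% / 77–80% for r = 0.5. Baseline adjustment can therefore offset the power loss. It leaves the SE ratio, and so the type I error, unchanged for a given ICC of the adjusted outcome.

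**The case against.** The strongest reply is that nothing in the article shows a positive ICC. The outcome is a timed walk measured by blinded assessors, the physiotherapists are trained in one programme, and dosage is tailored to the individual. All of this could keep class-level variation small, and at ICC 0.01–0.02 the inflation is slight. That stands, and the point is therefore conditional.

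The type I error argument also needs care. If the programme and its classes change nobody's outcome, individual randomisation protects the test. A simulated cohort effect shared by both arms, at ICC 0.10, gave 4.0% rejection. Inflation requires classes that differ in their effect while averaging zero.

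Three stronger readings are tempting and should not be adopted:

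- *Class or instructor effects are mistaken for a programme effect.* That would be a bias, whereas the calculation concerns variance only. The average contribution of class and instructor is part of a supervised group programme, and no model can separate it when controls have no class.
- *Each facility is a cluster of about 25 women (75/3), so even ICC 0.02 gives nearly 8%.* The article does not describe such clusters, and facility differences shared by controls do not inflate the test.
- *True power is about two thirds.* That is the t-test basis at ICC 0.10, not the planned ANCOVA.

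Two defences fail. The repeated-measures model does not link women in the same class. The analysis plan announced for each paper could add a class term, but the protocol article has already stated a model and a planning test that assume independence. A later plan also cannot fit a class effect if class and instructor were not recorded.

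**Conclusion.** The point holds in conditional form. The stated ANCOVA and the t-test sample size assume independence in a design where one arm is treated in classes, and nothing in the article cures this. For any positive within-class correlation given baseline, arising because classes differ in their effect, the standard error is too small.

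The size depends on an ICC that the article does not give and on whether classes are closed. It ranges from none at ICC 0 to 9–10% true alpha at ICC 0.10 with full closed classes. The top of that range should not be read as the expected value, since the accrual arithmetic points to smaller overlapping groups. Confidence is high for the direction given a positive ICC, and medium for the size. The change should be made, but the trial is not invalid without it.

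**What to change.** Record class and instructor for each exercise participant, with facility and term if entry is rolling. In line with intention-to-treat, women who never attend keep the class to which they were assigned.

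For the primary and secondary outcomes, fit a partially nested mixed model with:

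- fixed effects for baseline value and randomised group;
- a random class effect in the exercise arm only (instructor × facility × term if entry is rolling), with controls as singletons;
- residual variances specific to each arm;
- Satterthwaite or Kenward-Roger degrees of freedom.

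Report the ICC, and keep the simple ANCOVA as a sensitivity analysis.

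The cost is one identifier column and analysis-plan wording. The downside is a somewhat wider interval and an imprecise class variance, because 64–75 women in classes of 8–10 form only about 7–10 classes (64/10 = 6.4; 75/8 = 9.4). That is why small-sample degrees of freedom are needed.
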